#### 2.8.1. Primary outcome.

The pain subscale of the Western Ontario and McMaster Universities Osteoarthritis Index (WOMAC) will be used to assess knee pain over the past 48 hours. The WOMAC pain subscale is a patient’s self-assessed pain level consisting of 5 questions, ranging from 0 (asymptomatic) to 4 (very severe), with a total score ranging from 0 to 20, with higher scores indicating more severe pain.^[44,45]^ The intraclass correlation coefficient of the scale was 0.90, and the validity was 0.77.^[46,47]^ A previous study showed a minimum clinically important difference of 12% improvement from baseline.^[48]^

#### 2.8.2. Secondary outcomes.

Secondary outcomes are as follows:

NRS will be used to evaluate knee pain in the previous month. The NRS is a standard tool for the study of chronic pain. It is assessed on an 11-number scale from 0 (no pain) to 10 (severe pain),^[49]^ with 1.8 units having been reported as an minimum clinically important difference.^[50]^Health-related quality of life will be assessed with the MOS item short form health survey. There are 36 questions in total, and corresponding scores are obtained according to standardized weights. The scores are added to obtain the rough test score, and the final score is obtained by the conversion formula of the scoring operation specified by the scale. The total score ranges from 0 to 100, with higher final scores indicating higher quality of life.^[51,52]^Physical function assessment: The WOMAC physical function and stiffness subscale is used, with a total of 19 questions, and the score ranges from 0 to 76 points. The higher the score, the more severe the dysfunction.^[44,45]^Functional physical performance includes the timed up and go test (measured in seconds, shorter times indicate better function).^[53,54]^Adherence is measured at 12 weeks after the allocation by the ratio of the number of completed HXCR sessions to the total number of sessions.

Baseline assessments will be conducted after informed consent has been confirmed. The collected content included participant age (in years and based on age on ID card), gender, height, weight, BMI, education level, occupation, income level, hobbies and interests, marriage, smoking and drinking status, medical history, and level of physical activity (assessed by the International Physical Activity Questionnaire (IPAQ Short).^[55]^ During the course of the trial, if the participant’s symptoms worsen, they may be allowed to use the relevant drug for treatment. However, any medication use will be recorded in the medical record and diary.

### 2.9. Sample size

The calculation is carried out according to the standard for the sample size of noninferiority trials and the unified standard for clinical trial reporting.^[38,56]^ Based on the degree of reduction in WOMAC pain scores was used as an index to assess the improvement in symptoms of KOA with each type of exercise. The literature was reviewed to obtain the means and standard deviations of changes in pain scores in the three groups of patients with KOA,^[42,57]^ The sample content estimate formula shows that, for a significance level of 0.05 and a yielding power of 90%,

$$\begin{array}{l} n=\varphi^{2}\left[\sum_{i=1}^{k}S_{i}^{2}/k\;\right]/\left[\sum_{i=1}^{k}{\left({\bar{X}}_{i}-\bar{X}\right)}^{2}/\left(k-1\right)\;\right]\; \end{array}$$

the sample size consists of 20 participants in each group. With a 20% dropout rate taken into account, each group needs 24 enrolled participants.

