## 2. Methods

### 2.1. Aim

The aim of this randomized controlled trial is to directly compare the effects of two different exercise modalities, power cycling and quadriceps training combined with online guidance separately on KOA mitigation of pain in patients with KOA in a community, compared to the control group. We hypothesize that there will be a difference between these two rehabilitation strategies. Our secondary aim is to compare the effectiveness of two different exercise modalities on other outcomes, including quality of life, improvement of functional physical performance, adherence of participants.

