### 2.11. Randomization and blinding

After baseline measurement, participants will be randomized 1:1:1 to the power cycling group, quadriceps group or control group using simple randomization. A table of random numbers will be produced using the computer soft SPSS (V21.0). Write the random number assigned to each group on a piece of paper and place it in an opaque envelope. Based on the order in which participants were enrolled, an independent biostatistician will randomly distribute envelopes to participants. Physicians and physiotherapists will receive standardized training prior to the start of the study and will be randomly assigned to three groups during the trial. Participants won’t be blinded because of the nature of the intervention; instead, they will only know their own grouping. Evaluators, statisticians, and data managers will be blinded during the trial.

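### The 90% power in section 2.9 belongs to a three-group omnibus test, is mislabelled as noninferiority, and does not carry over to the hypothesised cycling-versus-quadriceps contrast

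*Protocol article*

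**What the plan says.** Section 2.1 (Aim) sets out a direct comparison of the two exercise programmes: "The aim of this randomized controlled trial is to directly compare the effects of two different exercise modalities". The same sentence also sets them against the control group. The hypothesis that follows concerns the two exercises only: "We hypothesize that there will be a difference between these two rehabilitation strategies".

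Section 2.9 (Sample size) opens with a different framework: "The calculation is carried out according to the standard for the sample size of noninferiority trials". It then describes its inputs ("The literature was reviewed to obtain the means and standard deviations of changes in pain scores in the three groups of patients with KOA"), its error rates ("for a significance level of 0.05 and a yielding power of 90" per cent), and a formula in which n equals φ² times the average of the group variances, divided by the sum of squared deviations of the k group means over k − 1. The result is that "the sample size consists of 20 participants in each group", and "With a 20% dropout rate taken into account, each group needs 24 enrolled participants".

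Section 2.11 confirms three equal arms: "participants will be randomized 1:1:1 to the power cycling group, quadriceps group or control group". Section 2.14 plans repeated-measures ANOVA, or Kruskal–Wallis if its assumptions fail. Section 2.9 gives no noninferiority margin, no group means or SDs, and no assumed difference between the two exercises.

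**The concern.** Three framings stand side by side: a two-arm difference (the hypothesis in 2.1), a three-group omnibus test (the formula in 2.9) and noninferiority (the label in 2.9). The formula has no place for a margin, so the label agrees with neither the formula nor the hypothesis.

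The formula's denominator pools all three means. The distance between control and the exercises therefore counts in full, and the omnibus test can have 90% power when the two exercises do not differ at all. The Introduction says that both regimens relieve pain and that a difference between them is controversial, so most of the spread could well come from control.

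At stake is how a non-significant cycling-versus-quadriceps result would be read. Set against an unqualified 90% and a noninferiority label, it could be taken as evidence that the two programmes are equally good, from a comparison that may have had little power.

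**Working it through.** **Inputs from the protocol article.** k = 3 arms, allocated 1:1:1 (2.11; k is read from the three-arm design, as 2.9 does not print its value); n = 20 evaluable per arm, α = 0.05, power 90% (2.9).

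**Assumptions, because the planning means and SDs are not printed.** n = 20 gives exactly 90% omnibus power; the SD σ is common to the arms; control is the worst arm; the contrast is tested by a two-sided t-test at 0.05 on one change score, without multiplicity adjustment.

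**Step 1: the plan's own figure.** Without means and SDs, n = 20 cannot be reproduced forwards, so it is solved backwards. Let S = Σ(μᵢ − μ̄)²/σ². The omnibus F test has 2 and 3 × 19 = 57 degrees of freedom and noncentrality 20·S. Setting its power to 0.90 gives:
- noncentrality 13.35, so S = 13.35/20 = 0.667
- Cohen's f = √(0.667/3) = 0.47
- φ = √(20 × 0.667/2) = 2.58

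Putting these back into the printed formula with σ = 1 gives 2.58²/(0.667/2) = 6.67/0.334 ≈ 20. This shows that the formula is the omnibus ANOVA formula. It does not verify the planning values.

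**Step 2: from the omnibus effect to the contrast.** Put control at 0, the better exercise at g and the weaker at r·g, in SD units. For means (0, r, 1) the sum of squared deviations is s(r), so g = √(0.667/s(r)). The difference between the exercises is d = (1 − r)·g. Power comes from the noncentral t with 38 degrees of freedom and noncentrality d·√(20/2).

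| r | s(r) | g | d | Power for cycling vs quadriceps |
|---|---|---|---|---|
| 1.00 | 0.667 | 1.00 | 0 | no difference to detect; rejection rate is α = 5% |
| 0.75 | 0.542 | 1.11 | 0.28 | 14% |
| 0.50 | 0.500 | 1.155 | 0.58 | 43% |
| 0 | 0.667 | 1.00 | 1.00 | 87% |

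In every row the omnibus test has 90% power. In the first row all of it comes from the gap to control.

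**Step 3: what 20 per arm can detect on the contrast.** Solving the same noncentral t for d gives 0.91 SD at 80% power and 1.05 SD at 90% power.

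**Step 4: sensitivity to the assumptions.**
- If control lay between the two exercises, midway, the exercises would differ by 1.155 SD and the contrast would have about 94.5% power. Nothing in the protocol suggests this ordering.
- If the analysis averaged three follow-up visits with an assumed between-visit correlation of 0.5 or 0.7, the variance would shrink by (1 + 2ρ)/3 = 0.667 or 0.80. The r = 0.50 case would then have d = 0.58/√0.667 ≈ 0.71 or 0.58/√0.80 ≈ 0.65, and power of about 59% or 51% instead of 43%.

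**The case against.** The strongest reply is that the omnibus calculation is not misplaced. The aim includes comparison with control, the trial has three arms, and section 2.14 plans three-group tests. This stands. A reader might infer that the omnibus test is the wrong test, or that a significant result from it would say nothing about the trial's question. The document does not support that: the test addresses part of the aim. What remains is that its power is not the power of one pairwise contrast, and that contrast is the only hypothesis stated.

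Second, the size of the shortfall cannot be established. The means and SDs are not printed, n = 20 may have been rounded up, and the formula allows unequal variances. This also stands. A reader might infer that the contrast certainly falls short of 90%, or that its power is 5%. Neither follows: if control lay between the exercises the contrast could exceed 90%, and 5% is the type I error rate when there is no difference, not a measure of low power.

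Third, the planned analysis uses repeated measures and the check uses one change score. Step 4 shows that this can raise the figures without bringing them to 90% in the case examined, so the pairwise values are illustrative.

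Fourth, the noninferiority wording occurs once, with no margin and no noninferiority hypothesis. A reader might infer that the sponsor intends a noninferiority conclusion, but nothing else in the article points that way. It is a wrong label, and for that reason easy to remove.

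**Conclusion.** The concern holds in a limited form. The noninferiority label in 2.9 is wrong as printed: it contradicts the formula beside it and the hypothesis in 2.1. The 90% is omnibus power over three groups including control, and it does not carry over to cycling versus quadriceps training.

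Under the assumptions listed in the working, power for that contrast is about 14% to 87% as the weaker exercise's share of the better one's gain falls from 75% to nothing. The range is conditional on those assumptions, so no single shortfall can be attributed to the plan. The fault lies in what the power statement claims. A reader might infer that the trial must be enlarged, but the document does not establish this, since the assumed difference between the exercises is unknown.

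**What to change.** In section 2.9:

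1. Delete the reference to the noninferiority standard and state that the calculation is for a test of difference.
2. State that the 90% refers to the three-group omnibus comparison of change in WOMAC pain. Do not add an assessment week: 2.9 names none, and Table 1 lists all four time points.
3. Add that, with 20 evaluable per arm and two-sided 0.05, the cycling-versus-quadriceps contrast has 80% power only for a difference of about 0.91 SD, and 90% only for about 1.05 SD, on a single change score. Mark this as illustrative, since repeated measures may alter it somewhat.
4. State that the contrast will be reported with its 95% confidence interval and that a non-significant result will not be read as equality or noninferiority.

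The cost is wording only, with no change in N. The downside is that the stated power for the main hypothesis becomes less favourable.

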### 2.8. Outcome measures

Outcomes for the trial will be chosen based on Osteoarthritis Research Society International recommendations.^[43]^ Table 1 summarizes the primary and secondary outcome measures. Outcomes will be measured at baseline (T_0_) and at 4 (T_4_), 8 (T_8_) and 12 (T_12_) weeks after the allocation (Table 2).

**Table 1 T1:** Outcomes of this study.

Measurements	Metric of measurement	Method of measurement	Time point of primary interest
Primary outcomes			
Self-reported pain	0–20 (higher scores indicate more serious pain)	Western Ontario and McMaster Universities osteoarthritis index (WOMAC) – pain subscale	baseline, and 4, 8, and 12 wk after allocation
Secondary outcomes			
Self-reported pain	0–10 (higher scores indicate more serious pain)	Numerical pain rating scale (NRS)	baseline, and 4, 8, and 12 wk after allocation
Quality of life	Standardized scores for every section (higher scores indicate more better social participation)	The MOS item short from health survey (SF-36)	
Self-reported function and stiffness	0–76 (higher scores indicate more serious dysfunction)	WOMAC – physical function and stiffness subscale	
Functional performance	Seconds (shorter time indicates better function)	Timed up and go test	
Adherence	0–100% (Higher ratios indicate better adherence)	The ratio of the number of completed HXCR sessions to the total number of sessions	12 wk after allocation

HXCR = Huaxi Cloud Rehabilitation, NRS = numerical pain rating scale, SF-36 = The MOS item short from health survey, WOMAC = Western Ontario and McMaster Universities Osteoarthritis index.

**Table 2 T2:** The participant timeline.

Time point	Study period				
	Enrolment	Allocation	Post-allocation		
	−T_1_	0	T_4_	T_8_	T_12_
Enrolment					
Eligibility screening	×				
Informed consent	×				
Allocation		×			
Interventions					
Education					
Medication					
Exercise					
Assessment					
Sociodemographic data	×				
Personal and medical history	×				
IPAQ Short	×				
Primary outcome			×	×	×
Secondary outcomes			×	×	×

IPAQ Short = International Physical Activity Questionnaire.

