### 2.14. Statistical analysis

Analyses will use an intention-to-treat analysis strategy. We will use one-way ANOVA to determine baseline comparability between groups for quantitative variable data. Baseline comparability between groups of categorical variable data will be determined using the chi-square test or other suitable nonparametric tests. Quantitative data will be expressed as the mean; if it follows normal distribution and homogeneity of variance, otherwise median is given. In statistical inference, if the data obeyed a normal distribution, and homogeneity of variance and satisfied spherical symmetry, repeated measures data analysis of variance was used; if the data did not obey a normal distribution or the variance was unequal, the Kruskal–Wallis H rank sum test was used for data analysis. SPSS (V21.0) will be used for data analyses. We considered *P* ≤ .05 to be statistically significant.

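### The 90% power in section 2.9 belongs to a one-way test on a single change score and does not carry over to the repeated-measures ANOVA named in section 2.14, where no decisive effect or visit is named

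*Protocol article*

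**What the plan says.** Section 2.9 (Sample size) takes from the literature the "means and standard deviations of changes in pain scores in the three groups of patients with KOA" and enters them into a printed formula: phi squared, times the average group variance, divided by the between-group variance of the means on k − 1. The calculation is made "for a significance level of 0.05 and a yielding power of 90" per cent, and the result is that "the sample size consists of 20 participants in each group". Enrolment is then set at 24 per arm for dropout. The means and SDs are not printed, nor is the visit at which the change is taken.

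Section 2.11 (Randomization and blinding) gives three arms, allocated 1:1:1. Section 2.8 fixes the visits: "Outcomes will be measured at baseline (T_0_) and at 4 (T_4_), 8 (T_8_) and 12 (T_12_) weeks after the allocation".

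Section 2.14 says that, given normality, equal variances and sphericity, "repeated measures data analysis of variance was used". If normality or equal variance fails, the Kruskal–Wallis test is used instead. The section does not say which effect of the ANOVA (group, time or group-by-time) or which visit carries the primary conclusion. For Kruskal–Wallis it does not say which value per person is ranked.

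**The concern.** The printed formula is the one for a completely randomised one-way ANOVA with k groups. It takes one value per person and yields a test with k − 1 = 2 numerator df. It holds no time factor, number of visits or time course.

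A repeated-measures ANOVA over four visits offers two overall tests that involve treatment:
- The group-by-time interaction, which is where a group difference in change appears. It has 2 × 3 = 6 df.
- The group main effect, which averages all visits, including the baseline, where randomised arms differ only by chance.

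Neither is the test that was sized. A reader of the protocol would take 90% as the chance that the named analysis detects the planned effect. That chance depends on how the benefit develops over 12 weeks and, for the main effect, on the correlation between visits. The protocol states neither.

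**Working it through.** **Inputs from the protocol.** k = 3 arms, 1:1:1; 20 completers per arm; alpha 0.05; power 90%; four visits; sphericity as the condition for the ANOVA.

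**Assumptions added here.** The sized change is baseline to week 12. The time course and the between-visit correlation are varied, because the protocol gives neither.

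**Step 1: the plan's own figure.** Without the literature means and SDs, n = 20 cannot be rebuilt, so the stated 90% at 20 per arm is taken at face value and the effect is solved from it. For F(2, 57) at alpha 0.05, 90% power needs noncentrality λ = 13.35. This corresponds to Cohen f = √(13.35/60) = 0.47 and phi = √(13.35/2) = 2.58.

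**Step 2: group-by-time test.** Let s_t be the share of the week-12 effect present at visit t, with s = 0 at baseline and s = 1 at week 12. Under sphericity the variance of a change between two visits is twice the within-person error variance, so no correlation has to be assumed:

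λ(group × time) = λ × 2 × Σ(s_t − s̄)², on 6 and 9 × (20 − 1) = 171 df.

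For steady build-up, s = 0, 1/3, 2/3, 1 and s̄ = 1/2. The squared deviations are 1/4, 1/36, 1/36 and 1/4, which sum to 5/9. The multiplier is 10/9, so λ = 13.35 × 10/9 = 14.83.

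| Share of week-12 effect at weeks 4 / 8 / 12 | Multiplier | λ | Power |
|---|---|---|---|
| 33 / 67 / 100% | 1.11 | 14.83 | 82.2% |
| 50 / 75 / 100% | 1.09 | 14.60 | 81.5% |
| 50 / 50 / 100% (lowest with both interim values free) | 1.00 | 13.35 | 77.3% |
| 60 / 85 / 100% | 1.16 | 15.53 | 84.2% |
| 25 / 75 / 100% | 1.25 | 16.68 | 87.1% |
| 50 / 100 / 100% | 1.375 | 18.35 | 90.5% |
| 100 / 100 / 100%, or effect only at week 12 | 1.50 | 20.02 | 93.1% |

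Simulation of the steady case (20,000 runs per setting; equal correlation 0.5, 0.7 and 0.9; three patterns of group means) gave about 82%. On the same formula, 24 completers per arm give 89.7% and 25 give 91.1%.

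**Step 3: group main effect.** With equal correlation r, and both variances scaled to the per-visit variance, the change variance is 2(1 − r) and the variance of a four-visit mean is (1 + 3r)/4. Hence

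λ(group) = λ × s̄² × 2(1 − r) / [(1 + 3r)/4], on 2 and 57 df.

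For steady build-up (s̄ = 1/2):
- r = 0.3: λ = 9.83, power 79%.
- r = 0.5: λ = 5.34, power 51%.
- r = 0.7: λ = 2.58, power 27%.

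**Step 4: sphericity relaxed.** With steady build-up and AR(1) correlation of 0.5 to 0.9, simulation of the group-by-time test gave 88% to 92% uncorrected and 86% to 89% with epsilon-corrected df.

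**Step 5: the fallback.** Kruskal–Wallis on the week-12 change is also a 2-df, one-value-per-person test. For normal data, with the usual relative efficiency of 0.955, λ = 13.35 × 0.955 = 12.74 and power is about 88.5%.

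**The case against.** The strongest reply is that section 2.14 never makes group-by-time the decisive test. A week-12 change contrast from the repeated-measures model is compatible with everything printed, and an analysis plan that is not shown may name it. Sizing on a simpler change-score test than the analysis model is also common practice. And WOMAC pain is a bounded 0–20 score, so the Kruskal–Wallis branch is realistic and, if applied to the week-12 change, lies close to the sized test.

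Much of this stands. The document does not fix the test, the 82% needs several conditions together, and no computation in section 2.9 is shown to be wrong. What remains is that section 2.9 prints the power of one test and section 2.14 names another analysis. Of the two overall treatment tests in that ANOVA, neither gives 90% under steady benefit with sphericity, and the main effect falls further short than the interaction.

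A reader might infer that the trial's true power is 82%, or that its type II error is 18% instead of 10%. The documents do not support this. They state no time course or correlation, and do not say that the sized change ends at week 12. An effect that is near complete early, or that appears only at the end, brings the interaction test to 90% or above. The 77% floor needs no gain at all between weeks 4 and 8. The AR(1) results fall outside the plan's own sphericity condition, but show how far the figure depends on it.

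**Conclusion.** The mismatch is real and its size is conditional. The 90% applies to a 2-df comparison of one change score and does not transfer to the four-visit repeated-measures ANOVA. For 20 completers per arm, a sized change from baseline to week 12, and sphericity:
- Group-by-time: about 82% under steady build-up, roughly 77% to 93% across time courses.
- Group main effect, steady build-up: about 79% to 27% at correlations of 0.3 to 0.7.
- Under AR(1) correlation with steady build-up, the group-by-time test keeps about 86% to 92%.

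No single one of these figures should be read as the power of the trial. The point is one of alignment between sections 2.9 and 2.14. It should be corrected, and it does not by itself call for more participants.

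**What to change.** In section 2.14, make the decisive test the one that was sized: the 2-df between-group comparison of WOMAC pain change from baseline to week 12. Take it as a contrast from the longitudinal model, or as Kruskal–Wallis on that same change if the assumptions fail. Keep the overall group-by-time test as supportive. In section 2.9, state that the change is from baseline to week 12 and that the 90% refers to this comparison. Replacing 90% with 82% in section 2.9 is not advised, since that figure would rest on a time course that the protocol does not state.

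The cost is wording in two sections, with no added participants or visits. The downside is that differences in the shape of the time course become supportive evidence only.

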### 2.4. Participants

We will recruit 72 patients with KOA. Participants’ inclusion criteria are: age ≥ 50 years with KOA, confirmed radiographically (Kellgren–Lawrence grade I–III), with 2021 Chinese Orthopedics Association guidelines for diagnosis and treatment of KOA clinical criteria^[39,40]^; knee pain (previous week) score of 3 to 6 on a numerical rating scale (NRS); able to use a smartphone to send messages and video calls; and able to communicate in Mandarin and understand Chinese characters.

Exclusion criteria are: having rheumatoid arthritis, gout or severe osteoporosis; preparing for knee replacement, other knee surgery in the next 6 months or knee surgery in the past 6 months; history of falls or fractures within the past 6 months; cancer; dementia or severe cognitive impairment; mental illness; diagnosis or suspicion of other conditions that limit exercise (e.g., stroke, heart failure, severe anemia, etc.); hypertension and diabetes not regularly medicated and monitored; other health problems that prevented them from participating in the project; and unable to sign informed consent.

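### The dropout allowance in section 2.9 multiplies where it should divide: 24 per group covers about 16.7% dropout, not the stated 20%

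*Protocol article*

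**What the plan says.** Section 2.9 (Sample size) of the protocol article bases the calculation on change in WOMAC pain in three groups, at significance level 0.05 and 90% power. The inputs come from published work: "The literature was reviewed to obtain the means and standard deviations of changes in pain scores in the three groups". Their values are not printed. The result before dropout is that "the sample size consists of 20 participants in each group". The allowance follows: "With a 20% dropout rate taken into account, each group needs 24 enrolled participants".

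Section 2.4 (Participants) carries this through as 3 x 24: "We will recruit 72 patients with KOA". The abstract gives the same total. Section 2.14 (Statistical analysis) adds: "Analyses will use an intention-to-treat analysis strategy". For the main inference it names repeated measures analysis of variance, with a rank test as the alternative.

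**The concern.** Three figures in section 2.9 belong together: 20 per group needed, 20% dropout, 24 per group enrolled. They do not agree. The allowance adds 20% of the number needed at the end, whereas dropout removes 20% of the number enrolled at the start. Adding 20% and then losing 20% does not return to the starting number.

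At stake is whether the enrolment target of 72 does what section 2.9 says it does, namely leave 20 per group after the dropout that the plan itself expects. The point needs no outside source, because all three figures are printed. It is also a stated figure that is wrong, not a detail left to a fuller document.

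**Working it through.** **Inputs.** From section 2.9: n = 20 per group before dropout, dropout d = 0.20, 24 enrolled per group, significance level 0.05, power 90%. From section 2.4: 72 in total. From the design: k = 3 groups.

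**Step 1: reproduce the plan's figure.** n x (1 + d) = 20 x 1.2 = 24 per group, and 3 x 24 = 72. This matches exactly, so the allowance was made by multiplication.

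**Step 2: what 24 per group leaves.** 24 x (1 - 0.20) = 19.2 per group, or 3 x 19.2 = 57.6 in total. The plan needs 20 per group, or 60 in total. The expected shortfall is 0.8 per group, 2.4 in total.

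**Step 3: the number that leaves 20.** n / (1 - d) = 20 / 0.8 = 25 per group, or 75 in total. Check: 25 x 0.8 = 20. The difference from the plan is 1 per group and 3 in total (3/72 = 4.2%).

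**Step 4: the dropout that 24 covers.** 1 - 20/24 = 0.167, that is about 16.7%.

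**Step 5: effect on power, as a range.** The figure of 20 cannot itself be re-derived, because the means and standard deviations are not given. A range follows from assumptions about how 20 arose, using the noncentral F distribution for a one-way comparison of three groups, with degrees of freedom 2 and 3n - 3 and noncentrality 3n x f², where f is the standardized spread of the group means.

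- *Assumption A: 20 per group gives exactly 90%.* Solving for f gives 0.472. Power is then 88.6% at 19.2 per group and 88.3% at 19. The loss is about 1.4 to 1.7 percentage points.
- *Assumption B: the formula returned just over 19 and was rounded up to 20.* Solving so that 19 gives 90% yields f = 0.485. Power is then 90.3% at 19.2 per group.

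At the stated 20% dropout, expected power therefore lies between about 88.6% and 90.3% under these two assumptions. Nothing in the document says which is nearer the truth.

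**The case against.** The strongest reply is that this is one participant per group and that the consequence for power has not been shown. Most of that stands.

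- **Power.** A reader might infer that 72 participants fail to deliver 90% power. The document does not support this. Without the means, standard deviations and unrounded result, power at 19.2 per group cannot be derived, and under Assumption B it still reaches 90%. Nor can one argue that 19 must fall below 90% because 20 is the smallest adequate number: section 2.9 gives 20 as the sample size and nowhere calls it the minimum. Even under Assumption A, the loss is small for a calculation that rests on literature inputs and an anticipated dropout rate.
- **Chance of reaching the target.** With independent 20% dropout and exactly 24 per group, the probability that all three groups keep at least 20 is about 10%, and that the total reaches 60 about 30%. A reader might take these as the size of the error. They are not, because the correct allowance of 25 per group gives only about 23% and 57% on the same measures. Much of the shortfall is ordinary binomial variation, which an allowance based on the expected number does not remove. Section 2.11 also specifies simple randomization, so 24 per group is not guaranteed in the first place.
- **Intention-to-treat.** Outcomes are measured at weeks 4, 8 and 12, so a participant who leaves late may still contribute data, depending on how missing values are handled. This limits the 19.2 to participants with complete data. It does not remove the point: the plan itself enlarged the sample for dropout, and the repeated measures analysis of variance named in section 2.14 ordinarily uses complete cases.

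None of this makes 24 the right answer to the question that section 2.9 poses.

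**Conclusion.** The allowance is wrong as written. At 20% dropout, 24 enrolled per group do not leave the stated 20; they leave 19.2 on average. The statement would be true for a dropout of about 16.7%, or with 25 enrolled per group. This rests only on the printed figures and on reading dropout as a share of those enrolled whose complete data are lost.

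The size is small: one participant per group, three in total. The effect on power is undetermined, at most about 1.4 percentage points at the expected 19.2 per group if 20 was just sufficient, and none if 20 was rounded up from about 19.2 or less. The finding is an internal inconsistency in a sample-size statement on which the trial relies, worth correcting because the correction is easy. It is not evidence that the trial is underpowered.

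**What to change.** Choose one of the following.

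1. Restate section 2.9 to say that 24 per group allows for about 16.7% dropout. This changes one figure and leaves the design and the total of 72 untouched.
2. Keep 24 per group and 20% dropout, state that about 19 per group are then expected with complete data, and recompute power from the sponsor's own means and standard deviations. The cost is one calculation. The 88.6% above should not be copied in, because it rests on a back-solved effect size that appears nowhere in the document.
3. Only if the sponsor wishes to keep both 20% dropout and 20 evaluable per group: correct the figures to 25 per group and 75 in total in the abstract, section 2.4 and section 2.9. The cost is three more participants.
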